##### APS Procedures

HTS providers called all elicited male sexual partners to inform them of their HIV exposure and offer HIV testing at the facility or a convenient location in the community. Initially, up to three attempts were made to notify the partners by phone; if unsuccessful, or if the female index client did not provide a phone number for the partner, HTS providers physically traced the partners in the community. If unsuccessful, two further attempts were made to notify the partners, either by phone or in-person. Partners were classified as lost to follow-up after six unsuccessful attempts or if a partner refused to meet with an HTS provider.

When implementing APS, HTS providers informed the partners of their potential HIV exposure without identifying the index participant. They asked the partners about their HIV testing history, provided HIV counseling, and offered HIV testing. Partners with a prior HIV diagnosis were asked about their current HIV care, and those who were out of care were counseled about the benefits and locations to access care. If a notification occurred over the phone, partners were encouraged to seek HTS at a study site or offered the opportunity for study staff to conduct a home-based HIV test. For partners who chose to seek HTS at a facility or safe space, the HTS provider who conducted the initial outreach generally contacted the partners via telephone to remind them of their testing appointment, rescheduled appointments as needed, conducted HTS, and documented test results, even if HTS was conducted at nonstudy sites. If HTS was completed at a nonstudy site by the partner, results were obtained via self-report. If a notification occurred as part of a home visit, partners were offered HTS after verbal consent per Kenya national guidelines [24]. When possible, HTS providers accompanied HIV-positive partners to the nearest HIV comprehensive care center for linkage to care.

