#### Data Analysis

##### Implementation Fidelity

Using a convergent mixed methods approach, we will examine the health facility characteristics (eg, location or staffing) associated with high fidelity to protocol elements and positive implementation outcomes by triangulating facility-level data with qualitative findings from the HTS provider IDIs. IDI audio recordings will be transcribed and analyzed by 2 independent coders using thematic content analysis to determine the key implementation fidelity themes using both deductive and inductive coding [29].

Descriptive statistics will be used to describe the characteristics of participants by county, type, and success of tracing attempts. Categorical variables will be described using counts and proportions, and continuous variables will be described using medians and IQRs. The time needed to conduct tracing attempts will be described using median and IQR and compared with the standard APS protocol to determine the fidelity to the protocol. Pareto charts based on the Pareto principle that 80% of the effects originate from 20% of the causes will be used to determine the tracing attempts through which most clients are successfully traced [30]. Data collected from HTS providers will be used to describe contextual factors.

In the multivariate analysis, successful tracing attempts (coded as either yes or no) will be the outcome of interest. We will consider two levels of data: individual level with clustering at the facility level. Log-binomial generalized estimating equations with exchangeable correlation structure and robust SEs will be used to estimate the relative risks and 95% CIs of successful attempts by the type of tracing attempt (phone vs physical). Variables associated with linking to care in these univariate analyses (*P*<.10) will be included simultaneously in the multivariate model. Moderators will not be included in this multivariate model; however, they will be used to provide context to the results of the quantitative analysis.

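### The phone-versus-physical tracing relative risk is confounded by the tracing sequence and by phone availability, so it cannot be read as the relative effectiveness of the two modes.

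*Protocol article*

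**What the plan says.** APS Procedures (Methods) sets the order of tracing. "Initially, up to three attempts were made to notify the partners by phone". Physical tracing in the community comes next, either because those calls failed or because the index client gave no number. Should this fail too, "two further attempts were made to notify the partners, either by phone or in-person". The end of tracing is also defined: "Partners were classified as lost to follow-up after six unsuccessful attempts or if a partner refused to meet with an HTS provider". The steps add up to the stated maximum if physical tracing in the middle is one attempt: 3 + 1 + 2 = 6. No rule is given for choosing the mode of the last two attempts.

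The Aim 2 Data Analysis section on Implementation Fidelity states that "successful tracing attempts (coded as either yes or no) will be the outcome of interest". On the structure of the data it says: "We will consider two levels of data: individual level with clustering at the facility level". A log-binomial GEE with exchangeable correlation and robust standard errors is to "estimate the relative risks and 95% CIs of successful attempts by the type of tracing attempt (phone vs physical". Covariates enter if they are associated with linking to care at P<.10. Attempt number and phone-number availability are not named.

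The Aim 2 Data Collection section says that frequency, type and success are recorded for each tracing attempt. The Discussion cites phone versus physical tracing among the process outcomes documented in the search for the factors most critical to implementation, and says the results will inform national and county scale-up.

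**The concern.** A relative risk of success by mode invites the reading that one mode works better. That reading needs the two sets of attempts to be made on comparable partners, and the sequence prevents this. Among partners with a number, attempts 1 to 3 are all by phone and attempt 4 is all physical, made only on those whom the phone attempts missed. Partners without a number contribute only physical attempts and may differ in other ways.

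The covariate rule does not repair this. It screens against linkage to care, which is not the outcome of this model, so attempt order could enter only by accident. Even if it did enter, attempts 1 to 4 offer no overlap of modes among partners with a phone, so adjustment there would be extrapolation. A programme that moved effort from one mode to the other on the strength of this figure could be responding to the sequence alone.

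**Working it through.** The article gives no sample size, power or expected relative risk for this contrast, so there is no stated figure to reproduce. The check asks what the pooled figure would be if the two modes were equally effective (true RR = 1) and the sequence were followed.

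**Inputs from the article:** up to 3 phone attempts, then physical tracing (1 attempt), then 2 of either mode; no-number partners start with physical tracing; tracing stops at success.

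**Assumptions (not in the article):** per-attempt reachability varies between partners as Beta(a, b); mode at attempts 5 and 6 is an even random split; no-number partners get three attempts; the share without a number is varied.

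**Step 1: phone attempts 1–3 against the first physical attempt, all partners with a phone, reachability shared between modes.** After k failures the success probability is a/(a+b+k). With a = b = 1.5:
- Success is 0.5 at attempt 1, 0.375 at attempt 2 and 0.3 at attempt 3; the fraction still untraced is 1 before attempt 1, 0.5 before attempt 2 and 0.3125 before attempt 3.
- Phone successes are 0.5 plus 0.1875 plus 0.09375, a total of 0.78125. Phone attempts are 1 plus 0.5 plus 0.3125, a total of 1.8125. The pooled success is 0.78125 divided by 1.8125, or 0.431.
- Attempt 4 (physical) is 1.5 divided by 6, or 0.25. RR is 0.431 divided by 0.25, or 1.72.
- The same formula gives 1.23 for a = b = 5 and 2.05 for a = b = 1.

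**Step 2: all six attempts and the no-number route, a = b = 1.5.** The fraction untraced is 0.21875 before attempt 4, then 0.16406 before attempt 5 and then 0.12891 before attempt 6; successes are 0.05469 at attempt 4, then 0.03516 at attempt 5 and then 0.02417 at attempt 6. Half of attempts 5–6 contributes 0.02966 successes over 0.14648 attempts to each mode.
- Phone: successes are 0.78125 plus 0.02966, or 0.81091; attempts are 1.8125 plus 0.14648, or 1.95898; pooled success is 0.414.
- Physical, partners with a number: 0.08435 successes over 0.36523 attempts.
- 10% without a number: successes are 0.9×0.08435 plus 0.1×0.78125, or 0.1540; attempts are 0.9×0.36523 plus 0.1×1.8125, or 0.5100; pooled success is 0.302 and RR is 1.37.
- 30%: 0.2934 successes over 0.7994 attempts, or 0.367; RR is 1.13.
- 60%: 0.5025 successes over 1.2336 attempts, or 0.407; RR is 1.02.
- If no-number partners get six attempts instead of three, the 30% figure is 1.20.

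**Step 3: reachability independent between modes.** Attempt 4 is then a fresh physical attempt at 0.5, so the Step 1 ratio becomes 0.431 divided by 0.5, or 0.86, favouring physical tracing.

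**Step 4: simulation over a wider grid** (400,000 partners per run; mean success 0.3 to 0.7; no-number share 0 to 0.6; Beta concentration a+b of 1, 2, 10 or no variation; true RR = 1):

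| Reachability | Share without a number | RR, phone/physical |
|---|---|---|
| No variation between partners | 0 to 60% | 0.99 to 1.00 |
| Shared between modes | 0 to 10% | 1.07 to 3.45 |
| Shared between modes | 30% | 1.02 to 1.32 |
| Shared between modes | 60% | 1.00 to 1.04 |
| Half of partners shared | 0 to 10% | 1.02 to 1.57 |
| Half of partners shared | 60% | 0.95 to 1.00 |
| Independent between modes | 0 to 60% | 0.79 to 1.00 |

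If the unit is instead the partner, classified by mode of last attempt, the RR was 1.02 to 2.99, above 1 in every run even without variation between partners, because most phone failures are moved into the physical group.

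**Step 5: attempts 5–6 only, partners with a phone** (mean 0.5, concentration 2, 10% without a number, mode random). Shared reachability: 0.166 phone against 0.168 physical at attempt 5, and 0.142 against 0.143 at attempt 6, so RR is about 1. Independent reachability: 0.200 against 0.334, and 0.183 against 0.295. The contrast is clean only if reachability is shared and mode is in effect random.

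**The case against.** A reader might infer that the figure is bound to favour phone, by 1.23 to 2.05. The documents do not support that. Step 1 gives every partner a number, makes reachability fully shared and leaves out attempts 5–6. A wrong or switched-off number need not mean that a man is hard to find at home, and first physical attempts on no-number partners follow no earlier failure. At attempt level the bias can be nil or can favour physical tracing. This stands, and it limits the claim about direction and size.

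A reader might also infer that the standard errors are wrong because repeated attempts on one partner have no level of their own. That largely fails: robust errors clustered by facility already allow for correlation among a partner's attempts when one facility does the tracing.

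It can fairly be said that a condensed article need not list candidate covariates, that this is a secondary fidelity analysis, that Pareto charts of attempts are already planned, and that the Discussion cites phone versus physical only as an example of a documented process outcome. These points lower the stakes. They do not remove the conflict, because the article itself fixes the contrast, the clustering and a covariate rule tied to a different outcome.

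**Conclusion.** The point holds as one of interpretation: under the stated sequence and model, the pooled phone-versus-physical relative risk cannot be read as the relative effectiveness of the modes. A bias towards phone is likely if difficulty of reach carries over between modes, but it is not certain. With a true RR of 1, the attempt-level figure ranged from 0.79 to 3.45 over the assumed values and was close to 1 when partners did not differ or when 60% lacked a number. Where it would fall in this study depends on four things the article does not give: the share of partners without a number, how far reachability is shared between modes, how mode was chosen at the last two attempts, and whether the unit is the attempt or the partner. All rates used here are assumptions.

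**What to change.** State the unit of analysis as the tracing attempt. Replace the pooled relative risk as the headline with (a) success per attempt, conditional on attempt number and phone-number availability, and (b) cumulative proportion reached after each step. Choose covariates for their relation to tracing success, not to linkage to care. Label any pooled phone-versus-physical relative risk descriptive, with a sentence saying that mode followed from earlier failure or lack of a number.

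A mode contrast at the two further attempts, where either mode was allowed, may be reported as secondary, with two caveats: mode there was not assigned at random, and it applies only to partners not reached by the earlier steps.

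The cost is a change of analysis wording and code. Type and success are already recorded for each attempt; it should be confirmed that attempt order and phone-number availability can be recovered from the same records. The downside is wider intervals and no single headline relative risk.

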##### Partner Participant Recruitment and Enrollment

Partners were aged ≥18 years. Recruitment and enrollment of partner participants took place during the tracing visit. Before testing for HIV, partners were invited to enroll in the study; however, they did not need to enroll to get tested. When possible, male partners who tested HIV positive were offered APS for their other female sexual partners.

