##### Participant Follow-Up

HTS providers made phone calls to assess linkage to and engagement in care and ART initiation for index clients and partners with HIV at 6 weeks and 6 months postenrollment. At 12 months postenrollment, participants were asked to make a physical visit to the comprehensive care center for clinical care consultation and to conduct an HIV viral load test. For all follow-up timepoints, participants who were not reached after three attempts by phone were physically traced.

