#### Outcomes

The effectiveness outcomes included (1) number of persons testing for HIV for the first time among all tested, (2) male partners who are newly diagnosed with HIV versus known to be living with HIV among all tested, (3) linkage to care and initiation of ART by 6 weeks and follow-up at 6 months for male partners with HIV and female index clients, and (4) suppression of plasma HIV RNA levels to <400 copies/µL at 12 months among male partners living with HIV and female index clients. We also monitor adverse events, including IPV and relationship dissolution.

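### The covariate rule for the successful-tracing model names linkage to care, not tracing success, as the variable to screen on

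*Protocol article*

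**What the plan says.** The text is in the protocol article, Methods, Aim 2, Data Analysis, Implementation Fidelity. For the multivariate analysis, "successful tracing attempts (coded as either yes or no) will be the outcome of interest". The effect to be estimated is the relative risk of success by type of attempt, phone versus physical, from log-binomial generalized estimating equations with clustering by facility. The selection rule follows directly: "Variables associated with linking to care in these univariate analyses", at P<.10, "will be included simultaneously in the multivariate model".

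Linkage to care is defined elsewhere. Aim 1, Outcomes, lists "linkage to care and initiation of ART by 6 weeks and follow-up at 6 months for male partners with HIV and female index clients". Participant Follow-Up says that providers telephone to "assess linkage to and engagement in care and ART initiation for index clients and partners with HIV at 6 weeks and 6 months postenrollment".

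**The concern.** A covariate screen is meant to find variables that matter for the outcome being modelled. This one names a different outcome, from a later step in the care cascade. A variable can affect whether a partner is found, and whether he is sought by phone or in person, without affecting whether an HIV-positive partner later links to care. The reverse is also possible.

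The group that can supply the screen is also narrower than the group the model describes, because a partner who is never found has no linkage status.

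What is at stake is the adjusted phone-versus-physical comparison. The Discussion counts phone and physical tracing outcomes among the process measures meant to show which factors matter most for scale-up, so the comparison is intended for use.

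**Working it through.** The plan states no sample size, power or error rate for this model, so there is no figure to reproduce. The check compares the sections, followed by simple counts and an illustration.

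**1. Outcome against screening variable.** The model's outcome is success of a tracing attempt (Implementation Fidelity). The screening variable is linkage to care (same paragraph). The sentence refers to these univariate analyses, but the section describes no analysis of linkage. The only regression before it is the one for successful attempts, so the reference has no matching antecedent.

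**2. Which traced-for partners have a linkage value.**
- Linkage is followed up after enrollment, in index clients and in partners with HIV (Participant Follow-Up; Aim 1, Outcomes).
- For partners, "Recruitment and enrollment of partner participants took place during the tracing visit" (Partner Participant Recruitment and Enrollment). The same section lets partners test without enrolling.
- For those not reached, "Partners were classified as lost to follow-up after six unsuccessful attempts or if a partner refused to meet with an HTS provider" (APS Procedures).

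A partner therefore has a linkage value only if he or she was reached, enrolled and HIV positive. A never-reached partner has none.

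**3. Rough size of that group**, from the Results as of March 2020.
- Enrolled partners: 3201 male + 1585 female = 4786.
- 6-week follow-up denominator, index clients and partners together: 2973.
- Assumption: all 1724 index clients are in that denominator. Partners in it are then 2973 − 1724 = 1249, and 1249 / 4786 = 26%.
- If fewer index clients were due, the share is higher. The arithmetic ceiling, with no index clients due, is 2973 / 4786 = 62%, which is not realistic.

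These shares are of enrolled partners. Never-reached partners are not in the denominator, and their number is not given.

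**4. Illustration of the mechanism, with assumed inputs.** The set-up was 1000 replicates of 4786 partners with one attempt each. The true phone-versus-physical relative risk was 1.00. One binary confounder, present in half of partners, doubled tracing success (60% against 30%), went with 80% against 40% phone use, and was unrelated to linkage. Of the partners reached, 40% were HIV positive. A second variable affected linkage only (95% against 85%). Screening used a chi-square test at P<.10, and adjustment used a Mantel-Haenszel relative risk.

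| | Screen on linkage | Screen on tracing success |
|---|---|---|
| Confounder kept | 10.2% of replicates | 100% |
| Linkage-only variable kept | 100% | not run |

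The mean relative risk was 1.34 without the confounder and 1.00 with it. The first can be checked by hand:
- Phone: the confounder is present in 0.8 / (0.8 + 0.4) = 2/3, so success is 2/3 × 0.60 + 1/3 × 0.30 = 0.50.
- Physical: it is present in 0.2 / (0.2 + 0.6) = 1/4, so success is 1/4 × 0.60 + 3/4 × 0.30 = 0.375.
- Ratio: 0.50 / 0.375 = 1.33.

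The 10.2% is close to the 10% false-positive rate of the screen, as expected for a variable set to be unrelated to linkage. The exercise shows how the rule can fail. It does not estimate anything in this trial.

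**The case against.** The strongest reply is that this is a wording slip. The phrase points back to analyses just described, and those concern successful attempts. If the authors meant tracing success, the predicted mis-adjustment never happens and one phrase needs correcting. That is plausible, but the text does not settle it: an analyst who follows the sentence screens on linkage, and one who departs from it has no stated rule.

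Several stronger readings are tempting, and the document does not support them:

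- **That linkage exists only for traced partners.** It is also measured in female index clients. The restriction holds only among the partners being traced.
- **That the screen contains only successes and so conditions on the outcome.** Success is recorded for each attempt, and up to six attempts are made, so a partner who was eventually reached can also contribute failed attempts. What is lost is the never-reached partners, not every failure.
- **That linkage can be screened in at most 18% of men.** The 12-18 per 100 in the Results counts new diagnoses among men tested. Linkage is defined for partners with HIV, and APS Procedures also covers those with a prior diagnosis.
- **That the model covers all elicited partners.** The article does not say so, and fidelity measurement began at least 12 months after site activation.
- **That P<.10 screening makes the final confidence intervals too narrow here.** Nothing in the document allows this to be quantified. Univariate screening is a conventional, if imperfect, choice, and the point does not depend on rejecting it.
- **That phone availability and attempt number should be forced into the model.** Under APS Procedures, phone comes first when a number exists and physical tracing follows, so these variables largely determine mode, and adjusting for them may leave little overlap. Nor does the article show that all such variables are recorded for never-reached partners, who have no enrollment record.

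**Conclusion.** Wrong as written; moderate severity. The selection rule names an outcome other than the one modelled, no section reconciles them, and never-reached partners cannot contribute to the screen as stated. Followed literally, the rule could omit factors tied to tracing success and mode and admit factors tied only to linkage.

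A reader might infer that the phone-versus-physical relative risks will be biased. The document supports only that they could be mis-adjusted; neither direction nor size can be derived from it. The 1.34 in the illustration depends wholly on its assumed confounder, and the 26% on the assumption that every index client was in the 6-week denominator.

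The reach is limited. This is one adjusted model within the Aim 2 fidelity work, beside descriptive statistics, Pareto charts and qualitative triangulation. The Aim 1 effectiveness outcomes are unaffected.

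**What to change.** In the selection sentence of Implementation Fidelity (Aim 2, Data Analysis), replace linking to care with successful tracing, so that the screen and the model share one outcome.

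Alternatively, drop the screen and prespecify covariates for tracing success, limited to variables recorded for all traced-for partners whether or not they were reached. County and facility characteristics are examples, since they can be known without contact with the partner.

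The first option costs one phrase. The second costs a short list and a check of which variables are recorded for partners never reached. Neither needs new data collection, and the article describes this analysis as still to be done.
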